### Go/no-go decision

After completion of phase 2, the results will be discussed in a meeting of the data safety monitoring board and the protocol committee. This moment is considered the “go/no-go” decision. Phase 3 of the LEOPARD-2 trial will only follow when the data safety monitoring board and the protocol committee have no concerns on patient safety. The conclusions of the data safety monitoring board and the protocol committee will be sent to the medical ethics review committee.

### Statistical aspects

#### Sample size calculation

The LEOPARD-2 trial is designed as a phase 2/3 superiority trial, hypothesizing that the postoperative time to functional recovery is shorter after minimally invasive than open pancreatoduodenectomy. Based on a systematic review and meta-analysis [4], a time to functional recovery of 14 days in the control group (open pancreatoduodenectomy) versus 11 days in the intervention group (MIPD) is expected, with a standard deviation of 5 days. Significance level (*α*) is set at 0.05 and power (1 − *β*) at 80%. Including 10% of cross-over from MIPD to open pancreatoduodenectomy, 2% loss to follow-up rate (based on previous surgical trials in the Netherlands), 10% of patients with metastasized disease (included, but oversampled to allow sufficiently powered per-protocol analyses), and after dividing by the asymptotic relative efficiency parameter of the Mann–Whitney U test (0.955) because of expected non-normally distributed data, 68 patients will be randomized in each group. Thus, in total 136 patients will be randomized within the LEOPARD-2 trial.

### Statistical analysis

Primary and secondary outcomes will be cross-checked with data from primary sources and a blinded adjudication committee (blinded for treatment allocation) will check them against the definitions, which were established before the start of this trial. Categorical variables will be compared using the chi-square or Fisher’s exact test as appropriate, and values will be expressed as proportions with corresponding risk ratios and 95% confidence intervals. The distribution of continuous variables will be determined using visual inspection and the Kolmogorov–Smirnov test. For comparison of normally distributed continuous variables the independent-samples *t*-test will be used and values will be expressed as means with standard deviations. Continuous non-normally distributed variables will be compared using the Mann–Whitney U test and values will be expressed as medians with interquartile ranges.

The primary endpoint is a time-to-event endpoint. However, considering that (a) the duration of recovery will most probably be censored in only 4% of patients at a maximum and that (b) taking the full length of the postoperative observation period as a proxy estimate for the time to recovery in these outlying patients will hardly affect the comparison of the study groups because of the non-parametric testing strategy with the Mann–Whitney U test and, finally, that (c) a power of 80% for a Kaplan–Meier analysis as its best alternative can only be achieved at the cost of a much higher and infeasible patient inclusion rate, we will analyze the data as if no censoring takes place. Additionally, the percentage of patients per study arm who do not recover during the observation period will be reported as a secondary outcome measure.

A difference with a two-tailed *P*-value < 0.05 will be considered statistically significant. A multivariable linear regression model will be used to assess potential differences in primary outcome between groups in the presence of potentially confounding factors. Linear mixed modeling will be applied to estimate differences between groups in successive EQ-5D-5 L and QLQ-C30 assessments over time. For exploratory purposes, a secondary analysis will be performed, comparing outcomes for patients with pancreatic ductal adenocarcinoma versus other disease, comparing completed minimally invasive (i.e. no conversion) versus open pancreatoduodenectomy and comparing time to functional recovery between minimally invasive and open pancreatoduodenectomy in complicated (Clavien–Dindo grade III or higher complication) and uncomplicated cases and for the impact of robot-assisted versus laparoscopic pancreatoduodenectomy. A non-inferiority analysis will be performed for Clavien–Dindo grade III or higher complications. The study has an 80% power (*α* = 0.05) to confirm non-inferiority of minimally invasive versus open pancreatoduodenectomy, when 15% fewer patients experience a clinically relevant complication in the intervention group than the control group (non-inferiority margin set at 8%). In the intervention group, robot-assisted procedures may be performed. The amount of robot-assisted procedures is expected to be less than 20%; these will be analyzed separately during cost-analysis.

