### Randomization

Eligible patients will be recruited at the outpatient clinic. Written informed consent must be provided before inclusion. Included patients will be randomized centrally by the study coordinators ([name] and [name]) using an online randomization module (ALEA, Clinical Research Unit, Academic Medical Center, Amsterdam, the Netherlands) in a 1:1 ratio between MIPD and open pancreatoduodenectomy (Fig. 1). Randomization will be stratified by center to balance differences in surgical procedure and general treatment regimen and by the preoperative probability of developing a postoperative pancreatic fistula: high risk (i.e. pancreatic duct diameter < 3 mm or body mass index > 25 kg/m^2^) versus low risk (i.e. i.e. pancreatic duct diameter ≥ 3 mm and body mass index ≤ 25 kg/m^2^). Stratification based on intraoperative patient characteristics was considered impossible. Permuted-block randomization will be used to provide treatment allocation in equal proportions, with block sizes ranging from 2 to 6, subject to random variation. This will be concealed to all investigators involved in the trial.

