### General treatment regimen

Postoperative care is similar in both arms per center and based on the enhanced recovery after surgery (ERAS®) principle, which includes pain control, early mobilization, and expansion of oral intake, as desired by the patient. Enhanced recovery is standard practice in participating centers. When patients are functionally recovered, they are essentially medically ready to be discharged. Discharge will however take place after shared decision making between the patient and the local treating team and may be delayed by arrangement of home care (e.g. for drain management).

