### Trial status

The first patient was randomized on 2 March 2016. LEOPARD-2 phase 2 has been completed and we continued with LEOPARD-2 phase 3. At the time of protocol submission (September 2017), four centers were actively recruiting patients for the trial, two centers were about to start recruiting, and 101 of 136 patients (74%) had been randomized. Inclusion is according to schedule.

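### The primary Mann–Whitney U test ignores the randomisation strata; if centre and fistula risk predict recovery, it is conservative and gives up power, though it stays valid

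*Protocol article*

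**What the plan says.** Under Randomization: "Randomization will be stratified by center to balance differences in surgical procedure and general treatment regimen and by the preoperative probability" of a postoperative pancreatic fistula. That second factor has two levels, "high risk (i.e. pancreatic duct diameter < 3 mm or body mass index > 25 kg/m^2^) versus low risk". Allocation uses permuted blocks, "with block sizes ranging from 2 to 6, subject to random variation". Under Trial status, "four centers were actively recruiting patients for the trial, two centers were about to start recruiting", which makes 8 to 12 strata.

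Under Statistical analysis the general rule is "Continuous non-normally distributed variables will be compared using the Mann–Whitney U test". The argument for setting censoring aside in the primary endpoint rests on the same test: "because of the non-parametric testing strategy with the Mann–Whitney U test". The sample size is also built on it, through the relative efficiency of 0.955. No stratified form is mentioned in any of these places.

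A multivariable linear regression "will be used to assess potential differences in primary outcome between groups in the presence of potentially confounding factors". The factors are not named, and this model is not the test on which the trial was sized.

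**The concern.** The reasons for stratifying make it plausible that the strata predict recovery. Centres are said to differ in surgical procedure and treatment regimen, and under General treatment regimen "Postoperative care is similar in both arms per center", so likeness of care is claimed within a centre, not across centres. Fistula risk is relevant because functional recovery requires that there be no active abdominal infection.

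If the strata are prognostic, stratified blocks nearly equalise them between arms. Most of the between-stratum variation then cannot contribute to the arm difference. Incomplete blocks leave a little. A plain Mann–Whitney U still counts all of that variation as chance, so its standard error is too large. P values come out too high and some information in the 136 patients goes unused. The article itself describes a much larger inclusion as infeasible, so efficiency in the analysis is worth having.

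**Working it through.** **1. The plan's own figure.** Inputs from Sample size calculation: 14 versus 11 days, SD 5, two-sided alpha 0.05, power 80%, cross-over 10%, loss to follow-up 2%, metastasised disease 10%, efficiency 0.955.

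n = 2 × [5 × (1.960 + 0.842) / 3]² = 43.6, so 44 per arm. The article does not spell out how the allowances combine. Treating cross-over as dilution of the effect and rounding up at each step gives 44/0.9² → 55; /0.98 → 57; /0.90 → 64; /0.955 → 68. The stated 68 per arm is reproduced for the unstratified test.

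**2. Approximation.** Let R² be the share of outcome variance explained by the strata. The article gives no value, so a range is assumed. With arms balanced within strata, the true variance of the arm difference is (1 − R²) times what the plain test assumes. Then:

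- true alpha of the plain test = 2 × [1 − Φ(1.96/√(1 − R²))]
- power, plain = Φ[(δ/SE − 1.96)/√(1 − R²)]
- power, adjusted = Φ[δ/(SE·√(1 − R²)) − 1.96]

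The diluted difference is δ = 3 × 0.9 = 2.7 days. Effective n = 68 × 0.98 × 0.90 × 0.955 = 57.3 per arm, SE = 5 × √(2/57.3) = 0.934, and δ/SE = 2.89.

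| R² | True alpha, plain | Power, plain | Power, adjusted |
|---|---|---|---|
| 0 | 5.0% | 82.4% | 82.4% |
| 0.05 | 4.4% | 83.0% | 84.3% |
| 0.10 | 3.9% | 83.6% | 86.1% |
| 0.24 | 2.5% | 85.7% | 91.2% |

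For the last row: 1.96/√0.76 = 2.25; (2.89 − 1.96)/0.872 = 1.067; 2.89/0.872 − 1.96 = 1.355.

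**3. Simulation.** Assumptions: six centres of unequal size, blocks of 2, 4 and 6, 70% high risk, normal errors, total SD 5. The adjusted test is rank ANCOVA: ranks regressed on arm, centre and fistula-risk stratum.

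- Null rejection of the plain test with 136 patients: about 4.5%, 3.4%, 2.9% and 2.0% at R² = 0.05, 0.10, 0.24 and 0.40. Rank ANCOVA stays near 5%.
- Power, plain versus adjusted, 68 per arm, at an assumed difference of 2.2 days: 70 versus 71% at R² = 0.05, 71 versus 74% at 0.10, 73 versus 81% at 0.24. At R² = 0 there is no material difference. The 2.2 days is not in the protocol; these figures show the gap between tests, not the trial's power.
- Power of the plain test at 2.7 days with about 57 per arm: 79, 80, 80 and 83% at R² = 0, 0.05, 0.10 and 0.24. This is slightly pessimistic, because 57 already includes the 0.955 factor.

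Monte Carlo error is about 0.7 points on power.

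**4. Skewed errors.** The article expects non-normal data. With four centres, log-normal errors, an assumed 2.0-day difference and a van Elteren test as the stratified comparator, null rejection of the plain test was 3.9%, 3.0% and 2.6% at R² = 0.05, 0.10 and 0.20. Power, plain versus stratified, was 86 versus 90%, 84 versus 90% and 80 versus 92%. The loss can therefore exceed the normal-error figures, again on assumed R².

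**The case against.** The strongest reply is that nothing is broken. The plain test holds type I error at or below 5%, the trial was sized for that test, and 68 per arm reproduces. A reader might infer from the conservatism that the trial falls short of its 80% power. The documents do not support that: at the diluted planning effect the plain test gives roughly 79 to 84% across the R² values examined, and in the approximation its power rises with R². This part of the objection stands.

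It also stands that the loss is conditional. A reader might take it that the plain test wastes power whatever the data. It does not: at R² = 0 there is no loss, and at 0.05 the gain from adjusting is about 1 point. No section quantifies how far centre or fistula risk predicts recovery, and enhanced recovery is described as standard in participating centres, which may keep centre effects small.

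A third argument is that stratifying the test and naming covariates belong in an analysis plan that is not shown. For the regression covariates this is fair, and their absence is not counted here as a fault. For the primary test it is weaker: the article names the test, defends it against Kaplan–Meier analysis and builds the sample size on it. That is a stated choice. Nor does the regression fill the gap, since it is not the primary test and is linear for an outcome expected to be non-normal.

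**Conclusion.** The point holds as a question of efficiency. The design uses centre and fistula risk and the primary test does not. If those factors explain 5, 10 or 24% of the variance in time to functional recovery, the plain test gives up about 1, 3 or 6 to 8 power points with normal errors, and its type I error drops to roughly 3% at 24%. Skewed data could make the loss larger. All of these sizes rest on assumed R² values and on the simulated centre mix.

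The test is not invalid, a significant result from it would not be in doubt, and the sample size is not shown to be inadequate. What is at stake is a real difference of moderate size being missed when the same patients could have shown it.

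**What to change.** Before the final analysis, and without sight of outcomes by arm:

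- Specify as the primary test a rank analysis adjusted for the randomisation factors: rank ANCOVA, or a proportional-odds model, with terms for arm, centre and fistula-risk stratum.
- Keep the unadjusted Mann–Whitney U as a sensitivity analysis, for continuity with the published plan.
- Name centre and fistula risk as covariates in the planned linear regression.

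With six centres the main-effects model has only seven terms besides the intercept's baseline (one for arm, one for risk, five for centre) if the intercept is not counted, which 136 patients carry easily. A fully stratified van Elteren test is a second choice: with 8 to 12 thin strata it lost about 1 to 3 points of power in simulation when the strata carried no information.

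Both factors are already recorded at randomisation, so no new data are needed and the programming is slight. The real cost is a documented amendment to the primary test when 101 of 136 patients had been randomised. Ward staff are not blinded, and phase 2 results were to be discussed with the protocol committee, so the amendment should record its date and that those who made it had not seen outcomes by arm.

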In the Netherlands, a platform for such a multicenter randomized trial has been created by the Dutch Pancreatic Cancer Group (DPCG), a nationwide multidisciplinary group including all 17 centers performing pancreatic surgery in the Netherlands. The DPCG followed the internationally accepted Idea, Development, Exploration, Assessment, and Long-term (IDEAL) study framework for surgical innovation for the implementation of minimally invasive pancreatic surgery in the Netherlands [8–10]. Since 2014, the DPCG successfully implemented minimally invasive distal pancreatectomy in all Dutch pancreatic centers within the LAELAPS (longitudinal assessment and realization of laparoscopic pancreatic surgery) project [11]. Thereafter, the DPCG initiated a similar nationwide training program for laparoscopic pancreatoduodenectomy (the LAELAPS-2 project) [12]. This program included detailed technique description, video training, and proctoring sessions (on-site and off-site) by (inter)national experts. Analysis of outcomes of 114 MIPDs performed within LAELAPS-2, in the first four DPCG centers that performed >20 MIPDs, showed an 11% conversion rate, a 43% Clavien–Dindo III or higher complication rate, and a 4% complication-related 90-day mortality [12]. Hereafter, a structured training program in robot-assisted pancreatoduodenectomy using the Pittsburgh approach (the LAELAPS-3 project) was implemented [13]. Based on these outcomes and the IDEAL study framework [8–10], it was decided that a randomized controlled trial was indicated in those centers that performed at least 20 MIPDs.

The LEOPARD-2 trial follows the LEOPARD trial on minimally invasive versus open distal pancreatectomy [14] but has a phase 2/3 design to assess patient safety more closely. The aim of the LEOPARD-2 trial is to compare time to functional recovery after surgery, complications, quality of life, and costs after MIPD versus open pancreatoduodenectomy, within an enhanced recovery setting.

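### The stated 80% power makes no allowance for the up to 4% of patients expected not to recover; on the sizing's own normal-theory basis, 4% in both arms brings it to about 74%

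*Protocol article*

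**What the plan says.** In the protocol article, the Sample size calculation states that "a time to functional recovery of 14 days in the control group (open pancreatoduodenectomy) versus 11 days in the intervention group (MIPD) is expected", with SD 5 days, α 0.05 and 80% power. The Statistical analysis section makes the test two-sided: "A difference with a two-tailed *P*-value < 0.05 will be considered statistically significant". The sample size is then raised for four things: 10% cross-over from MIPD to open surgery, 2% loss to follow-up, 10% metastasized disease, and division by 0.955 for the Mann–Whitney test. The result is 68 per arm, 136 in total.

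The Statistical analysis section accepts that the primary outcome is a time to event but analyses it without censoring. Its first reason is that "the duration of recovery will most probably be censored in only 4% of patients at a maximum". Its second is that entering such patients at the end of the observation period "will hardly affect the comparison of the study groups because of the non-parametric testing strategy with the Mann–Whitney U test". Its third is that a Kaplan–Meier analysis with 80% power would need too many patients. Data collection and follow-up puts outcome collection at up to 3 months after surgery, about 90 days.

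**The concern.** The power statement and the analysis rule describe different data. The power is worked out as if every analysed patient has a recovery time with SD 5 days. The analysis adds a group, up to 4% on the plan's own figure, who never reach the endpoint and share the top tied rank in both arms. A rank test limits how far an extreme value can pull the result. It does not remove the dilution: these patients bring the probability that a MIPD patient recovers sooner than an open patient closer to one half.

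Power is also one of the plan's grounds for preferring this analysis to Kaplan–Meier, so the power of the chosen method should be stated on the data it will meet. Otherwise a non-significant primary result would be read against a power that is somewhat too high.

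**Working it through.** **1. Reproduce the printed sample size.** Inputs from the Sample size calculation: difference 14 − 11 = 3 days, SD 5, α 0.05 (two-sided), power 80%.

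- Normal formula: n = 2 × (1.960 + 0.842)² × 5² / 3² = 43.6, so 44 per arm.
- Mann–Whitney efficiency: 44 / 0.955 = 46.1, so 47.
- 10% cross-over: 47 / 0.90² = 58.02, so 59.
- 2% loss: 59 / 0.98 = 60.2, so 61.
- 10% metastasized disease: 61 / 0.90 = 67.8, so **68**.

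The printed figure is reached with rounding up at each step, and no step covers non-recovery. The evaluable number implied is 68 × 0.98 × 0.90 = 60 per arm.

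**2. Can SD 5 already include the non-recovered?** Take 4% at day 90 and the rest around 12.5 days with SD 5. The total SD is √(0.96 × 25 + 0.04 × 0.96 × 77.5²) = √(24 + 230.6) = 16.0 days. So SD 5 fits recovered patients only. This is inferred; the article does not say so.

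**3. Closed form for the loss.** Let θ be the probability that a MIPD patient recovers sooner, counting ties as one half. If a share p in each arm is tied at the maximum:

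θ − 0.5 = (1 − p)² × (θ₀ − 0.5), where θ₀ applies to recovered patients.

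The null variance hardly changes (tie factor 1 − p³). Starting from exactly 80%:

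- p = 4%: Φ(2.802 × 0.96² − 1.960) = Φ(0.622) = 73.3%.
- p = 2%: Φ(2.802 × 0.98² − 1.960) = Φ(0.731) = 76.7%.

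If the same 4% were simply absent, power would be Φ(2.802 × √0.96 − 1.960) = 78.4%. Most of the loss therefore comes from the ties at the maximum, not from a smaller n. Returning to 80% by numbers alone would take a factor of 1/0.96⁴ = 1.18, about 80 per arm.

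**4. Simulation.** Tie-corrected Mann–Whitney test, two-sided 0.05; normal times, means 14 and 11, SD 5; 10% of the MIPD arm drawn from the open distribution; 60 per arm; equal shares set to day 90; 60,000 trials per cell.

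| Non-recovered in each arm | Power |
|---|---|
| 0% | 81.3% |
| 1% | 79.5% |
| 2% | 77.8% |
| 3% | 76.3% |
| 4% | 74.2% |

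Repeat runs put the 0% case at about 81% and the 4% case at 73.6% to 74.2%.

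**5. Sensitivity, from 0% to 4% in both arms.**

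| Setting (10% cross-over throughout) | 0% | 4% |
|---|---|---|
| Normal, 67 per arm (metastatic patients carry the full effect; 68 × 0.98) | 85.3% | 78.8% |
| Weibull, 60 per arm | 82.9% | 75.9% |
| Gamma, 60 per arm | 86.4% | 80.5% |
| Lognormal, 60 per arm | 91.1% | 85.8% |

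The article gives no split by arm. In the normal case with 60 per arm, 5% open and 3% MIPD gives 80.2%; 3% open and 5% MIPD gives 67.4%.

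**6. Does the proxy value matter?** Moving it from day 90 to day 365 leaves power unchanged within simulation error (about 74% both ways), because the ranks are the same.

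**The case against.** Four counter-arguments deserve weight.

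- **Shape.** The plan chose the Mann–Whitney test because it expects non-normal data, and 74% rests on normal data. This stands as a limit on the level: gamma and lognormal times keep power at or above 80% with 4% non-recovered. It does not rescue the stated figure, because 0.955 is the normal-shift efficiency and the build-up claims no gain from skewness. The loss is still 5 to 6 points in those cases. A reader might infer that the trial's power simply is 74%; the documents do not support that unconditional statement.
- **Metastatic patients.** They are to be included, and whether they carry the full effect is not stated. Counting them gives about 78–79% at 4%, so neither n is the plan's single answer.
- **The proxy.** A reader might infer that the second reason is false and should go. Read as a statement about which late value to enter, it is right: any value at or beyond the end of follow-up gives the same ranks. What it does not cover is the effect of non-recovery itself. Nor do the inputs contradict each other, provided SD 5 describes recovered patients.
- **The 4% ceiling.** A reader might add "a 4% complication-related 90-day mortality" in the training series (Background) to the 2% loss and infer 4–6%. The documents do not show that those deaths and losses come before recovery, the mortality figure is for MIPD only and equals the stated maximum, and the 2% has already been taken out of the 60 per arm. Equally, 4% is an upper figure, so the loss at 4% is the upper end on the plan's own terms.

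**Conclusion.** The power statement is incomplete as written. On the basis used for sizing (normal shift, SD 5, efficiency 0.955, 10% cross-over, about 60 evaluable per arm), the plan's maximum of 4% non-recovered, assumed equal in both arms, takes power to about 74%; 2% takes it to about 78%.

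The size of the loss is the firm part: 5 to 8 points at 4%, whatever shape or n was tried. The level is conditional: about 74–80% across the less skewed settings and the two readings of the metastatic allowance, and about 86% if times are lognormal. An unequal split between arms could move it either way. The finding does not question the sample size, the choice of test or the rule for entering non-recovered patients.

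**What to change.** Keep N at 136 and leave the test as it is.

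- **Sample size calculation:** state that the 80% is conditional on all analysed patients recovering and that SD 5 is taken to describe recovered patients. Add the power at the plan's own 4% maximum with its assumptions (equal shares in both arms, 10% cross-over, whether metastatic patients carry the effect): about 74–80%, higher if times are strongly right-skewed.
- **Statistical analysis:** limit the second reason to the choice of proxy value, which does not change the ranks. Add that non-recovery itself lowers power by about 5 to 8 points at 4%.
- **Leave the 4% maximum as it stands.** The documents give no basis for replacing it with 4–6%.

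The cost is wording and a slightly less favourable power figure. No extra patients or data are needed, so the change remains possible although 101 of 136 patients had been randomized when the article was submitted.

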### Data collection and follow-up

Baseline characteristics will be collected before randomization using standardized case record forms; this comprises age (years), sex, performance status (Karnofsky score), WHO physical status, American Society of Anesthesiologists physical status, body mass index (kg/m^2^), Malnutrition Universal Screening Tool score, medical history, symptoms and duration of symptoms, conclusion preoperative imaging, tumor size on imaging, TNM (tumor, node, metastasis) stage on imaging, pancreatic duct diameter on imaging (measured at the level of the portal vein), tumor involvement of other organs, preoperative expected diagnosis, preoperative biliary drainage, and use of somatostatin analogs. Operative characteristics include pancreatic texture (soft versus firm), pancreatic duct diameter (mm), and type of anastomoses. Primary and secondary outcome measures will be collected after randomization up to 3 months postoperatively using standardized case record forms by the local treating physicians or the study coordinators. The case record forms and the database will be cross-checked with source data by the study coordinators. Patients will be asked to complete validated questionnaires on postoperative days 2, 4, and 6 (EQ-5D-5 L) and at 2 weeks, 4 weeks, and 12 weeks postoperatively (EQ-5D-5 L and QLQ-C30). Please see Fig. 1. Long-term follow-up results of the LEOPARD-2 trial (including complications and quality of life) will be published separately.

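### The supportive adjusted analysis of time to functional recovery is a linear regression that treats follow-up length as a recovery time, which the plan justifies only for a rank test

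*Protocol article*

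**What the plan says.** Four statements in the protocol article bear on this.

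- **Distribution.** The Sample size calculation section inflates the sample by the Mann–Whitney efficiency factor "because of expected non-normally distributed data".
- **Patients who do not recover.** The Statistical analysis section calls the endpoint time-to-event but drops censoring. It expects that "the duration of recovery will most probably be censored in only 4% of patients at a maximum", and its approach is "taking the full length of the postoperative observation period as a proxy estimate for the time to recovery in these outlying patients". Under Data collection and follow-up, outcomes are collected "up to 3 months postoperatively", so the proxy value is about day 90.
- **Why this is thought harmless.** One statistical reason is given for the proxy: it "will hardly affect the comparison of the study groups because of the non-parametric testing strategy with the Mann–Whitney U test". (The article also argues that a Kaplan–Meier analysis would need too many patients. That concerns feasibility, not the effect of the proxy.)
- **Adjusted analysis.** Further on in the same section: "A multivariable linear regression model will be used to assess potential differences in primary outcome between groups in the presence of potentially confounding factors". No transformation, robust version, censoring method or exception for the proxy values is stated.

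**The concern.** A rank test registers only that a non-recovered patient is among the slowest, so it matters little whether the value entered is 60 or 90. A linear regression uses the value itself. Among recoveries averaging 11 to 14 days with an SD of 5, an entry of 90 is an outlier with great influence on the arm's mean and on the residual variance. The article's defence of the proxy therefore stops at the Mann–Whitney test, yet the same data go into the regression.

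At stake is how the adjusted result will be read. Its purpose is to show whether the treatment difference persists after adjustment. If a handful of proxy values decides the estimate, it may seem to contradict a sound primary result, or may exaggerate it, for reasons unrelated to confounding.

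**Working it through.** **Inputs from the article.** Means 14 (open) and 11 (minimally invasive) days, SD 5, two-sided alpha 0.05, power 80%, 68 per arm, at most 4% not recovered, outcome collection to 3 months (taken as 90 days).

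**The plan's own figure.** n = 2 × [5 × (1.960 + 0.842)/3]² = 43.6, so 44 per arm. Rounding up at each step: 44/0.955 → 47; /(1 − 0.10)² for cross-over → 59; /0.98 → 61; /0.90 → 68. This reading of the allowances reproduces 68, and the sample size is not in dispute.

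**Shift per patient.** With 12.5 as the midpoint of the two means, (90 − 12.5)/68 = 1.14 days; from the open mean, (90 − 14)/68 = 1.12. A net imbalance of three such patients gives 3 × 1.14 = 3.4 days, more than the 3-day design effect. Four percent of 136 is about 5 patients. If five fall to either arm by chance, an imbalance of three or more (4–1 or 5–0) has probability 2 × (5 + 1)/32 = 0.375.

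**Variance.** With a share p at day 90, SD² = (1 − p) × 25 + p(1 − p) × 77.5². At p = 0.04 this is 24.0 + 230.6 = 254.6, so SD = 16.0. The proxy values supply 230.6/254.6 = 91% of the variance (83% at 2%, 71% at 1%).

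**Power by formula.** The standard error is SD × √(2/68).
- No patient at day 90: 3/0.857 = 3.50, power 94%.
- 4% at day 90: the mean difference is 3 × 0.96 = 2.88 and the standard error 2.74; 2.88/2.74 = 1.05, power 18%. The same formula gives 47% at 1% and 30% at 2%.

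**Power by simulation.** Assumptions: gamma recovery times with the design means and SD, 68 per arm, non-recovery equally likely in both arms, and an unadjusted t-test standing in for the treatment term of the regression (no gain from covariates).

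| Share at day 90 | Linear comparison | Mann–Whitney |
|---|---|---|
| 0% | 94% | 92–96% throughout |
| 1% | 57% | |
| 2% | 39% | |
| 4% | 20% | |

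Repeat runs differ by up to about 3 points. At 4%, the linear estimate has the wrong sign in roughly 13–15% of trials despite a true 3-day benefit. Under the null at 4%, the linear comparison rejects in 4.5% of trials.

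**Sensitivity to the proxy day.** If the period were shorter (assumption), formula power at 4% would be 36% for day 60 and 80% for day 30.

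**Sensitivity to who is at day 90.** If all of the 4% were entered between days 5 and 30 (assumption), linear power is about 88%; between days 5 and 60, about 67%. With 1% at day 90 and 3% between days 5 and 60 it is 45%. Mixes with more patients at day 90 go down to about 32%.

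**The case against.** The strongest reply is that nothing confirmatory depends on this model. The planned test of the primary endpoint is the unadjusted Mann–Whitney test, and the article gives the regression no role in declaring success. Four percent is a stated maximum, and with nobody at day 90 the linear comparison performs well. An analysis plan that is not shown might add a transformation. All of this stands, and it limits the point to a supportive analysis. It does not remove it: the article fixes both the proxy and the linear model, and 1% (one or two patients in the trial) already costs much of the power. A log transformation would recover only part: simulated power is 75% at 4% and 86% at 2%.

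It is also fair to object that placing the whole 4% at day 90 is the worst case. Some of these patients may have died, and the article reports 4% complication-related 90-day mortality in its training cohort (Background). If deaths were entered on earlier days, the loss would be smaller, as the last sensitivity check shows.

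Three stronger readings are tempting but unsupported:
- A reader might infer that early deaths enter at their death day and so pull the estimate the other way. The article states no rule for deaths.
- A reader might infer that covariates will be picked by observed imbalance. The article says nothing about selection, and the covariate list is ordinary analysis-plan detail.
- A reader might infer that the regression will be the only estimate in days with a confidence interval. The article promises no interval for it and does not exclude others.

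**Conclusion.** The point holds for the supportive covariate-adjusted analysis and no further. The plan's one statistical reason for entering non-recovered patients at follow-up length applies to ranks and fails for a linear model of the same outcome. At the plan's own 4% ceiling, power of the linear comparison is about 20% if all these patients sit at day 90 and about 32% to 88% if some or all are entered earlier. These figures rest on a 90-day period, gamma-shaped recovery times, equal non-recovery in both arms and no precision gain from covariates.

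A reader might infer that the trial's main conclusion is at risk or that false positives are inflated. Neither follows: Mann–Whitney power stays at 92–96%, and the linear type I error is near nominal. What suffers is the precision and stability of the adjusted estimate. The change is worth making because it is cheap and avoids an apparent conflict between the primary and adjusted results.

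**What to change.** Replace the linear regression with an adjusted model that uses the same ordering as the primary test. A suitable choice is a proportional-odds model on ordered recovery days, with non-recovered patients in the worst category and an explicit statement of where deaths before recovery are placed. Adjust for the factors already used in the Randomization section, centre and preoperative fistula risk. Report the odds ratio with its confidence interval and, alongside it, the unadjusted Hodges–Lehmann shift in days with its interval, so that an effect in days remains available.

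The cost is a change of wording before the data are analysed, with no extra patients or data. The downside is that this model no longer gives an adjusted mean difference in days, and its odds ratio relies on the proportional-odds assumption, which should be examined. Other rank-consistent models would also serve; what matters is that day 90 is not treated as an observed recovery time.
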